### Withdrawal criteria

2.11

The patients presenting the following conditions will be withdrawn from this study:

occurring serious adverse reactions so as to be inappropriate to continue the study;occurring severe complications or condition deterioration so as to need emergency measures;not following the prescribed treatment or without complete data so as to affect the efficiency of evaluation.

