#### Primary outcome measurement

2.8.1

The primary outcome will be assessed using PSQI, a self-rating questionnaire designed to assess overall sleep quality. It includes 19 self-rating items and 5 other-rating items. It evaluates sleep quality according to the following 7 aspects over the past month: sleep duration, sleep efficiency, daytime dysfunction, delays in falling asleep, use of medications to sleep, sleep disorders, and overall sleep quality. Each aspect is rated 0 to 3 points, and the accumulated scores of the 7 aspects are 0 to 21 points. The higher score indicates poorer sleep quality. The reliability and validity of the Chinese version have been verified.^[11]^ The PSQI will be evaluated at baseline, during treatment period (at 4, 8, and 12 weeks) and follow-up period (at 1, 3, and 6 months).

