### Patients’ safety

2.10

All patients will accept blood routine, hepatic, and renal functions tests to identify and exclude the patients with severe heart, liver, or kidney disease after the recruitment and before the random allocation. The acupuncture will be discontinued if patients occur any adverse effects. Adverse events (AE) indicate any adverse medical events that occur in the patients regardless of events are related to the operation or experimental drug in the study. The patients will be informed to contact the doctor to diagnose and treat the AE. Fainting, allergy, and pain may appear in the acupuncture clinical trials.^[15]^ If faints occur, the needles will be pulled out immediately, patients will be returned to supine position, given warm or sugar water, and rest until complete recovery. If allergy or pain occurs, needles are taken out immediately and patients are treated according to the specific situation.

The serious AE (SAE) includes death, life-threatening conditions, severe or persistent incapacity or disability, hospitalization, extension of hospitalization time, and potentially serious events. Whether relating to the trial, any SAE or relevant events must be reported to the research unit within 24 hours. The researcher is responsible for recording and reporting all AE and SAE that occurred during the trial (including a 12-week treatment period and a 6-month follow-up period) since the date of signing the informed consent.

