### Sample size

2.12

PSQI scores after the end of acupuncture are taken as the sample size calculation index. The statistical significance level is set as 0.05, and 80% is taken as the statistical power. A previous study showed the PSQI score of patients with perimenopausal insomnia is 8.62 ± 2.93 in the acupuncture group and 14.76 ± 3.35 in the sham acupuncture group.^[8]^ According to this, the following formula is used to calculate the estimated sample size: N = 2[(t_α/2_ + t_β_)S/δ]^2^. The combined standard deviation is assumed as 1.5, and δ is 0.5 times of the standard deviation. β is 0.8, and α is 0.05. Considering the dropout rate of 20%, at least 79 cases will be required in each group. Therefore, we need to recruit a total of 158 patients for this randomized controlled trials (RCT).

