### Statistical analysis

2.13

The statistical analysts will be blind to the patients’ group allocation. All data, including data of the withdrawing patients during the trial, will be analyzed based on intention-to-treat. Two different researchers will participate in the data entry, and all data are entered twice to guarantee the accuracy. The statistical analysis will be performed using SPSS 24.0 software (IBM, Armonk, NY, USA). The measurement data will be expressed as mean ± standard deviation or median and separately compared using *t* test and Wilcoxon rank-sum test. The count data will be shown as number and percentage, and compared using chi-squared or Fisher exact test. The change of PSQI score between the 2 groups at different time points will be compared by repeated-measures analyses of variance. The difference before and after treatment in each group will be determined using paired *t* test. All statistical tests are 2-tailed, with *P* values ≤.05 as statistical significance.

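### Withdrawing patients from the study for non-adherence or incomplete data is not reconciled with the promised intention-to-treat analysis

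*Protocol article*

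**What the plan says.** Section 2.11 (Withdrawal criteria) opens with "The patients presenting the following conditions will be withdrawn from this study" and lists three conditions. The first two concern serious adverse reactions and severe complications or deterioration. The third is "not following the prescribed treatment or without complete data so as to affect the efficiency of evaluation".

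Section 2.10 (Patients' safety) uses different language for stopping treatment: "The acupuncture will be discontinued if patients occur any adverse effects". The article can thus distinguish ending acupuncture from leaving the study, and section 2.11 speaks of the latter.

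Section 2.13 (Statistical analysis) states: "All data, including data of the withdrawing patients during the trial, will be analyzed based on intention-to-treat". For the primary outcome it adds: "The change of PSQI score between the 2 groups at different time points will be compared by repeated-measures analyses of variance".

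Section 2.8.1 and Table 1 schedule PSQI at baseline, at weeks 4, 8 and 12, and at 1, 3 and 6 months after treatment. Section 2.12 bases the sample size on the PSQI score after the end of acupuncture.

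**The concern.** An intention-to-treat comparison needs outcomes from all randomised patients, whatever treatment they took. A rule that ends study participation because treatment was not followed, or because data are incomplete, acts after randomisation and on features that can be related to both arm and outcome. The course is 36 sessions (3 a week for 12 weeks). One arm receives penetrating needles with electrical stimulation at two points; the other receives a non-penetrating placebo needle without current. Adherence could plausibly differ between them, and within an arm it could depend on how the patient is sleeping.

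The qualifier about affecting the evaluation is a judgement. Section 2.11 gives it no threshold and names nobody to make it.

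If later PSQI values are missing for a group selected in this way, the comparison no longer fully rests on randomisation. An analysis plan written later can choose how to handle missing values, but it cannot recover scores that were never taken.

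**Working it through.** **1. The sections side by side.** Take a patient judged at week 5 to be non-adherent to a degree that affects evaluation.

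- Under section 2.11 the patient leaves the study.
- Under section 2.13 the baseline and week-4 PSQI scores stay in the analysis.
- The scores due at weeks 8 and 12 and at months 1, 3 and 6 are five of the seven scheduled, and they include the post-treatment score on which the trial is sized. No sentence says they are still collected.
- Repeated-measures ANOVA in its conventional form uses only patients with every time point. In that form the patient would drop out of the PSQI comparison despite the intention-to-treat statement.

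**2. The plan's own figure, and why power is not the issue.** Inputs from section 2.12: SD 1.5, δ = 0.5 × 1.5 = 0.75, α = 0.05, power 80%, dropout 20%. Section 2.13 makes tests two-sided.

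- n per group = 2 × [(1.960 + 0.842) × 1.5 / 0.75]² = 62.8, rounded up to 63.
- 63 / (1 − 0.20) = 78.75, rounded up to 79 per group, or 158 in total. This reproduces the plan.
- Normal-approximation power at δ = 0.75 is 88% with all 79 per group and 80% with 63. It is 75% with 55 (about 30% loss) and 68% with 47 (about 40% loss).

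The 20% allowance covers the planned loss of numbers. It gives no protection against selective loss.

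**3. Illustration of the possible bias.** Assumptions, none of them in the documents: the worst-adhering fraction f of one arm is lost and contributes nothing to the analysis; adherence and outcome are jointly normal with correlation r. The mean of those kept then differs from the mean of the whole arm by

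shift (in SD) = r × φ(q) / (1 − f), with q = Φ⁻¹(1 − f).

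For f = 0.10, φ(q)/(1 − f) = 0.1755 / 0.90 = 0.195. For f = 0.20, it is 0.2800 / 0.80 = 0.350.

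| f | r | shift (SD) | points (× 1.5) | share of δ = 0.75 |
|---|---|---|---|---|
| 0.10 | 0.3 | 0.058 | 0.09 | 12% |
| 0.10 | 0.5 | 0.097 | 0.15 | 19% |
| 0.20 | 0.3 | 0.105 | 0.16 | 21% |
| 0.20 | 0.5 | 0.175 | 0.26 | 35% |

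**4. Cross-check with a simpler model.** If a fraction w of one arm is lost and their mean differs from that of the patients kept by d SD, the shift is w × d. For w from 0.05 to 0.20 and d from 0.25 to 1, this runs from 0.0125 to 0.20 SD. That is 0.02 to 0.30 points, or 2.5% to 40% of δ. The range in step 3 lies inside this one.

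The direction is not fixed. A higher PSQI score is worse, so losing poor sleepers makes an arm look better and losing early responders makes it look worse. The sign also depends on which arm loses more.

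**The case against.** The strongest reply is that the authors foresaw withdrawals and said what happens to the data. Section 2.13 includes withdrawing patients expressly, and no sentence excludes a randomised patient from analysis or discards a recorded score. That stands. A reader might infer that section 2.11 flatly contradicts intention-to-treat, or that the trial is a per-protocol analysis under another name. The text does not support either reading: a per-protocol analysis excludes non-adherers by rule, while section 2.13 keeps their data.

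Nor does section 2.11 say that assessments stop. Table 1 runs to 6 months without an exception for withdrawn patients, and procedures after withdrawal may sit in a full protocol that is not shown. This part stands only partly. The ordinary meaning of withdrawal from a study is that its visits end, and section 2.10 shows that the article had other words for stopping acupuncture alone.

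Three further inferences go too far.

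- One missed visit does not by itself cost all of a patient's data. The criterion requires an effect on the evaluation, and values already recorded are kept.
- It is not established that non-adherence differs between arms. Patients are blinded, and the sham uses the same points, a connected device and the same 30-minute retention. A difference is plausible, not documented.
- The two SDs in the cited perimenopausal study (2.93 and 3.35) pool to 3.15, which turns the shift into 0.18 to 0.55 points. Setting that against 0.75 suggests roughly 25% to 75% of the planned difference. This mixes scales, because 0.75 is half of an SD of 1.5. In SD units the comparison is 0.058 to 0.175 against 0.5, which is again 12% to 35%.

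**Conclusion.** The concern holds as an unreconciled conflict between sections 2.11 and 2.13. On its plain reading, section 2.11 leaves later PSQI values unmeasured for patients selected by adherence or data completeness, so the promised intention-to-treat comparison cannot be fully carried out. The issue is bias; the sample size is unaffected.

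The illustrative size is 0.09 to 0.26 PSQI points, or 12% to 35% of δ. It rests on loss of 10% to 20% from one arm only, an adherence-outcome correlation of 0.3 to 0.5, the plan's SD of 1.5, and an analysis to which the lost patients contribute nothing. Similar selective loss in both arms would largely cancel, and a method that used the scores recorded before withdrawal could reduce the shift. The conflict itself follows from the text and does not depend on these figures.

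**What to change.** Amend section 2.11 and align section 2.13 with it:

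- Remove non-adherence and incomplete data as grounds for leaving the study.
- State that stopping acupuncture does not end outcome assessment.
- Keep collecting PSQI at every Table 1 visit from all randomised patients who still consent, and record withdrawal of consent separately from stopping treatment.
- If an adherence-based analysis is wanted, use adherence only to define a supplementary per-protocol set.

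The two safety-related withdrawal criteria and the rule in section 2.10 are left as they are. The cost is a short amendment and some extra follow-up contacts for a self-rated questionnaire. No additional patients are needed. The change has to come while the scores can still be collected, because it cannot be made good at analysis.

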### Patients

2.2

The hypertension patients with insomnia will be recruited in Bao’an People's Hospital, Shenzhen from September, 2021 to March, 2022. Each patient uses 1 to 3 antihypertensive drugs (calcium antagonist, angiotensin converting enzyme inhibitor/angiotensin receptor blocker, diuretics, or β-blocker). On the basis that patient's diet, physical activity, and use of antihypertensive drugs remain unchanged, they will accept a 12-week treatment. Each patient is required to sign the informed consent before the treatment, and accept a 6-month follow-up (visits at 1, 3, 6 months).

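### The third withdrawal criterion removes non-adherent or incomplete-data patients from the study, so on its natural reading the intention-to-treat PSQI analysis would lack their later scores

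*Protocol article*

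**What the plan says.** Section 2.11 (Withdrawal criteria) opens with "The patients presenting the following conditions will be withdrawn from this study" and lists three conditions. The first two concern safety: serious adverse reactions, and complications or deterioration needing emergency measures. The third is "not following the prescribed treatment or without complete data so as to affect the efficiency of evaluation". Section 2.10 (Patients' safety) has separate wording for stopping acupuncture alone when an adverse effect occurs.

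Section 2.13 (Statistical analysis) states: "All data, including data of the withdrawing patients during the trial, will be analyzed based on intention-to-treat". For the primary outcome it adds: "The change of PSQI score between the 2 groups at different time points will be compared by repeated-measures analyses of variance".

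Section 2.8.1 (Primary outcome measurement) sets the schedule: "The PSQI will be evaluated at baseline, during treatment period (at 4, 8, and 12 weeks) and follow-up period", the follow-up visits being at 1, 3 and 6 months. Section 2.2 (Patients) asks every patient to accept those follow-up visits. Section 2.12 (Sample size) says: "PSQI scores after the end of acupuncture are taken as the sample size calculation index".

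**The concern.** Following the prescribed treatment and having complete data are both determined after randomisation. A rule that takes patients out of the study on those grounds works against an as-randomised comparison, because the people removed are selected by what happened to them after allocation. Each patient is due 3 × 12 = 36 sessions, so some non-adherence is foreseeable.

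The reasons for missing sessions may also differ by arm. Active needling penetrates the skin and two points carry current (section 2.6). The sham needle does not penetrate and no pulse is delivered (section 2.7). Discomfort could drive more loss in the active arm, or lack of benefit could drive more in the sham arm. Either would leave the PSQI scores that remain unrepresentative of the groups as randomised. An analysis plan can choose how to treat missing scores, but it cannot recover scores that the protocol chose not to collect.

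**Working it through.** **1. The plan's own figure.** Inputs from sections 2.12 and 2.13: two-sided α 0.05, power 80%, SD 1.5, δ = 0.5 × 1.5 = 0.75, dropout 20%.

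n = 2 × [(1.96 + 0.8416) / 0.5]² = 62.8, rounded up to 63 per arm. 63 / 0.8 = 78.75, rounded up to 79 per arm, 158 in total. This reproduces the stated figure, which is not in dispute. The planned allowance is 79 − 63 = 16 patients per arm.

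**2. What withdrawal means.** Section 2.10 speaks of discontinuing acupuncture, and section 2.11 speaks of withdrawal from the study. Since the article words the two differently, the natural reading of 2.11 is exit from the study, including its visits. This is an inference: 2.11 does not say in terms that PSQI assessment stops. No other section says that it continues.

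**3. Scores lost on that reading.** The PSQI is due at baseline, 4, 8 and 12 weeks, and 1, 3 and 6 months: 7 assessments.

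| Withdrawn | Scores lost | Week-12 score lost? |
|---|---|---|
| before week 4 | 6 | yes |
| between weeks 4 and 8 | 5 | yes |
| between weeks 8 and 12 | 4 | yes |
| after the week-12 assessment | at most 3 | no |

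Section 2.11 sets no time at which the criterion is judged, so all rows are possible.

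**4. Illustration only.** Suppose that only patients who stay are analysed. Let wA and wS be the shares lost in the active and sham arms, and gA and gS the PSQI points by which lost patients would have scored worse than stayers in the same arm. The stayers' difference (sham minus active) is then the true difference plus wA·gA − wS·gS. With a common gap g and a true difference of 0.75:

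| Loss, active / sham | g = 0 | g = 0.75 | g = 1.5 |
|---|---|---|---|
| 20% / 20% | 0.75 | 0.75 | 0.75 |
| 25% / 15% | 0.75 | 0.825 | 0.90 |
| 15% / 25% | 0.75 | 0.675 | 0.60 |

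Equal loss is harmless here only because the gap is the same in both arms. A gap of 1.5 in one arm and 0 in the other shifts the result by 0.20 × 1.5 = 0.30.

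With no true effect, about 59 and 67 stayers (79 × 0.75 and 79 × 0.85) and SD 1.5, a two-sided t test at a nominal 5% rejects in 5.0%, 5.9% or 8.6% of trials for a bias of 0, 0.075 or 0.15 points. If the SD were about 3.15, the pooled value √[(2.93² + 3.35²)/2] of the SDs cited in section 2.12, the same 0.15 points would give 5.8%.

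None of the loss splits or gaps has a source in the documents. The illustration also spends the whole 20% allowance, which must cover every kind of loss, not only the third criterion.

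**The case against.** The strongest reply is that section 2.13 already brings withdrawn patients' data into the analysis, and that section 2.10 has adverse events recorded through the 6-month follow-up with no exception for withdrawn patients. A condensed article may leave procedures after withdrawal to the full protocol. This stands to the extent that the end of PSQI collection must be called an inference. It does not remove the conflict: including data is not the same as collecting it, and the point concerns a rule that the article states, not a detail that it omits.

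It is also fair to say that patients lacking complete data have already missed assessments. For them the rule costs only later visits that they would have attended, a share that is not known.

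Three stronger readings are tempting and are not supported:

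- A reader might infer that the trial will be biased towards acupuncture. The documents give no loss rate by arm, the direction could be either way, and equal, uninformative loss gives none.
- A reader might infer that the repeated-measures analysis will discard every withdrawn patient. Standard software does so for any missed visit under any withdrawal rule. Handling of missing visits is commonly left to an analysis plan, which is not shown, so this carries no weight here.
- A reader might extend the criticism to the first two criteria. They address safety, and nothing in the documents shows them to be wrong.

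**Conclusion.** The concern holds in limited form. The third criterion is a stated rule that, on its natural reading, stops primary-outcome collection because of post-randomisation behaviour, and so undercuts the intention-to-treat analysis promised in section 2.13. For an affected patient the cost is 4 to 6 of 7 scores, among them the end-of-treatment score behind the sample size, if withdrawal comes before week 12, and at most 3 if it comes later. How many patients would be affected, and whether their loss would favour either arm, cannot be determined from the documents. The bias and error-rate figures show what assumed splits would do and are not estimates of the rule's effect. The 20% dropout allowance protects power against expected losses, but not the comparison against losses that differ in kind between arms. The sponsor should correct this, because the remedy is simple and no later analysis can supply scores that were never collected.

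**What to change.** In section 2.11, delete the third criterion as a reason for study withdrawal and write: 'Patients who do not follow the prescribed treatment, or who miss an assessment, remain in the study; the PSQI is collected at all remaining Table 1 visits unless the patient withdraws consent.' Leave the first two criteria and the section 2.10 safety stop unchanged.

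The cost is the amendment wording and the remaining self-rated questionnaires for these patients. If the entire 20% allowance (16 per arm) were third-criterion withdrawals during treatment, that would be 16 × 4 = 64 to 16 × 6 = 96 questionnaires per arm. The true number should be lower, since the allowance also covers other losses. The sample size of 158 does not change.

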### Sample size

2.12

PSQI scores after the end of acupuncture are taken as the sample size calculation index. The statistical significance level is set as 0.05, and 80% is taken as the statistical power. A previous study showed the PSQI score of patients with perimenopausal insomnia is 8.62 ± 2.93 in the acupuncture group and 14.76 ± 3.35 in the sham acupuncture group.^[8]^ According to this, the following formula is used to calculate the estimated sample size: N = 2[(t_α/2_ + t_β_)S/δ]^2^. The combined standard deviation is assumed as 1.5, and δ is 0.5 times of the standard deviation. β is 0.8, and α is 0.05. Considering the dropout rate of 20%, at least 79 cases will be required in each group. Therefore, we need to recruit a total of 158 patients for this randomized controlled trials (RCT).

### Statistical analysis

2.13

The statistical analysts will be blind to the patients’ group allocation. All data, including data of the withdrawing patients during the trial, will be analyzed based on intention-to-treat. Two different researchers will participate in the data entry, and all data are entered twice to guarantee the accuracy. The statistical analysis will be performed using SPSS 24.0 software (IBM, Armonk, NY, USA). The measurement data will be expressed as mean ± standard deviation or median and separately compared using *t* test and Wilcoxon rank-sum test. The count data will be shown as number and percentage, and compared using chi-squared or Fisher exact test. The change of PSQI score between the 2 groups at different time points will be compared by repeated-measures analyses of variance. The difference before and after treatment in each group will be determined using paired *t* test. All statistical tests are 2-tailed, with *P* values ≤.05 as statistical significance.

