**Methods and analysis::**

This study is a randomized, double-blind (patients and evaluators), and placebo-controlled clinical trial to investigate the effect of acupuncture in hypertension patients’ insomnia management. We will recruit 158 hypertension patients suffering from insomnia in Bao’an People's Hospital, Shenzhen and randomly assign them into treatment group (antihypertensive drugs + acupuncture) and control group (antihypertensive drugs + sham acupuncture) in a 1:1 ratio. The patients will receive acupuncture 3 times a week for 12 weeks, and then a 6-months follow-up will be conducted after the treatment. The primary outcome is the Pittsburgh Sleep Quality Index. The secondary outcomes include sleep parameters, blood pressure dropping, sleeping pill dosage, Rating Depression Scale score, and Self-Rating Anxiety Scale score. The primary outcome will be evaluated at baseline, 4, 8, and 12 weeks, and 1, 3, and 6 months following the end of treatment. The secondary outcomes will be assessed at baseline and 12 weeks of the treatment period.

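### Between-group analyses name no baseline covariate although baseline PSQI and secondary scores are collected; adjusting for them would gain precision at no cost

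*Protocol article*

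**What the plan says.** The protocol article (Statistical analysis, 2.13) fixes three methods for continuous data.

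- Between groups, in general: "The measurement data will be expressed as mean ± standard deviation or median and separately compared using" the t test and the Wilcoxon rank-sum test respectively.
- PSQI over time: the change of score is compared between groups by repeated-measures analysis of variance.
- Within each group: before and after values are compared by paired t test.

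No covariate is named for any of these.

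Baseline values are available. The Primary outcome measurement section and Table 1 place PSQI at baseline, at 4, 8 and 12 weeks, and at 1, 3 and 6 months of follow-up. For the rest, the abstract states: "The secondary outcomes will be assessed at baseline and 12 weeks of the treatment period". Table 1 agrees, with secondary outcomes marked at allocation and at 12 weeks.

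The Sample size section (2.12) uses a post-treatment score: "PSQI scores after the end of acupuncture are taken as the sample size calculation index". Its formula has no baseline term.

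**The concern.** A baseline value of the same scale is usually the best single predictor of the follow-up value. Comparing raw follow-up scores ignores it and leaves explainable variation in the error term. Subtracting it, as a change score does, gives it a fixed weight of one, which is too much whenever the correlation between baseline and follow-up is below one. Entering it as a covariate lets the data set the weight, and also corrects the estimate for chance baseline imbalance.

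For the continuous secondary outcomes, the t or Wilcoxon test is the only between-group comparison named, and the text does not say whether it is applied to week-12 values or to changes. Those two choices can differ in power, and ANCOVA removes the need to choose. For PSQI, baseline enters through change or through the time factor, but not as a covariate.

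At stake is precision, and therefore power and the width of the confidence intervals. It can be improved without another patient, visit or measurement.

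**Working it through.** **Inputs from the Sample size and Statistical analysis sections**

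- "The statistical significance level is set as 0.05, and 80% is taken as the statistical power", and "All statistical tests are 2-tailed".
- "The combined standard deviation is assumed as 1.5, and δ is 0.5 times of the standard deviation", so δ = 0.5 × 1.5 = 0.75 and the standardised effect is d = 0.5.
- "Considering the dropout rate of 20%, at least 79 cases will be required in each group", hence "we need to recruit a total of 158 patients".
- The correlation ρ between baseline and follow-up is not given. It is an assumption, shown below at 0.3, 0.5 and 0.7.

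**Step 1: reproduce the plan's figure**

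n = 2[(1.960 + 0.842) × 1.5 / 0.75]² = 62.8, so 63 per group. Then 63 / 0.8 = 78.75, so 79 per group and 158 in total. The stated figure reproduces for an unadjusted comparison of post-treatment scores. (The t-distribution version gives 64, then 80 per group.)

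**Step 2: variance factors for one follow-up score**

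With equal variances at baseline and follow-up, relative to the raw-score comparison:

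- raw follow-up score: 1
- change score: 2(1−ρ)
- ANCOVA: 1−ρ²

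The ratio of ANCOVA to change is (1−ρ²) / [2(1−ρ)] = (1+ρ)/2, which is below 1 for any ρ below 1. ANCOVA is therefore more precise than both alternatives for every ρ strictly between 0 and 1.

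**Step 3: power for a single week-12 comparison**

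The effective standardised effect is 0.5 / √(variance factor), with 63 evaluable per group and a two-sided 5% t test.

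| ρ | Raw | Change: factor, power | ANCOVA: factor, power |
|---|---|---|---|
| 0.3 | 79.5% | 1.40, 65.3% | 0.91, 83.1% |
| 0.5 | 79.5% | 1.00, 79.5% | 0.75, 89.5% |
| 0.7 | 79.5% | 0.60, 94.9% | 0.51, 97.4% |

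The normal approximation gives 80.1% raw and 83.7%, 90.0% and 97.6% for ANCOVA, which is the same picture.

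**Step 4: does the gain persist with repeated PSQI measurements?**

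This step is illustrative. Assume that all seven PSQI measurements are equally correlated, with equal variances and a constant effect over the six post-baseline visits. The variance factor for the mean of the six visits is (1+5ρ)/6. For the mean change it is (1+5ρ)/6 + 1 − 2ρ. With baseline as covariate it is (1+5ρ)/6 − ρ².

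- ρ=0.3: 0.417 + 1 − 0.6 = 0.82 for mean change; 0.417 − 0.09 = 0.33 adjusted.
- ρ=0.5: 0.583 + 1 − 1 = 0.58 for mean change; 0.583 − 0.25 = 0.33 adjusted.

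Under these assumptions adjustment lowers the variance of the repeated-measures comparison too.

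**The case against.** **Validity.** Under 1:1 randomisation the unadjusted tests are unbiased and hold their type I error, because chance imbalance is already reflected in the standard error. The planned 80% power is met on the protocol's own inputs. This stands in full, and it makes the point an improvement rather than an error.

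**The PSQI analysis.** A reader might infer that PSQI rests on unadjusted t or Wilcoxon tests, and that at ρ=0.5 the plan therefore gives up the equivalent of 63 / 0.75 = 84 against 63 evaluable patients per group. The article does not support that. Its PSQI-specific sentence names repeated-measures analysis of variance of change, which already uses baseline and several visits. Under the assumptions of step 4, mean change over six visits would itself reach about 87% power at ρ=0.3 and 95% at ρ=0.5, above the single-visit ANCOVA figures. The week-12 table therefore does not measure the PSQI loss. The principle remains: on the same assumptions, adjusted variance is lower still.

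**Size of the gain.** It depends on an unstated ρ. Entry requires PSQI above 5, and restricting the baseline range tends to lower the correlation. At ρ=0.3 the gain over raw scores is under 4 percentage points. This stands.

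**Scope.** Model terms are often left to an analysis plan, and none is shown here; one could add covariates. A bare silence would be no finding, and the absence of any mention of stratification is not held against the article. But the article does name its between-group methods, and those contain no baseline term.

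**Coverage.** Not every secondary outcome clearly has a usable baseline. Estazolam use is described as recorded during the trial, so a pre-treatment dose is doubtful. Blood pressure is framed as a fall, already a change measure, though baseline can still be a covariate.

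**Conclusion.** The point holds as a free improvement. The named between-group analyses are valid but less precise than baseline-adjusted ones, although the baseline values are scheduled. It is clearest for the continuous secondary outcomes, where the unadjusted t or Wilcoxon test is the only between-group comparison named. For PSQI the accurate statement is repeated-measures analysis of variance of change with no baseline covariate.

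For a single week-12 score with 63 evaluable per group and d = 0.5, power is about 80% raw, 83% with ANCOVA at ρ=0.3 and 90% at ρ=0.5. The gain is modest at the low end and useful from about 0.5 upwards. These figures rest on an assumed ρ, equal variances at the two times and the protocol's own effect size. They should not be read as the power lost in the PSQI analysis, nor as a sign that 158 patients are too few.

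**What to change.** - **PSQI:** analyse with baseline PSQI as a covariate, either by ANCOVA at week 12 or by a mixed model of the post-baseline visits with baseline and baseline-by-visit terms.
- **ISI, SAS, SDS, blood pressure and sleep parameters:** use ANCOVA of the week-12 value with the corresponding baseline value as covariate. For blood pressure, modelling the fall or the week-12 value gives the same treatment estimate once baseline is in the model.
- **Sleeping pill dosage:** leave out of the adjustment unless a pre-treatment value is recorded.
- **Reporting:** give adjusted mean differences with 95% confidence intervals, and keep the unadjusted tests as sensitivity analyses.
- **Timing:** fix the covariates before unblinding, so that their choice cannot depend on the results.

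The cost is a few lines of analysis text. No patient, visit or measurement is added, and the sample size can stay as it is.
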